# The MOMANT study, a caregiver support programme with activities at home for people with dementia: a study protocol of a randomised controlled trial

**DOI:** 10.1186/s12877-022-02930-x

**Published:** 2022-04-07

**Keywords:** Dementia, Informal caregiver, Psychosocial intervention, Randomized controlled trial, Activities at home

## Abstract

**Background:**

Because of the expected increase in the number of people with dementia, and the associated social and economic costs, there is an urgent need to develop effective and cost-effective care for people with dementia and their caregivers. The intervention proposed here combines two approaches to caregiver support that have shown to be effective in empowering caregivers, i.e., multiple components for caregiver support and actively engaging caregivers to involve the person with dementia in activities at home. The aim is to investigate whether the intervention is effective in improving quality of life in the caregiver and the person with dementia. A further aim will be to investigate whether this intervention can improve caregivers’ feeling of competence, experience of caregiving, and mood.

**Methods:**

The study design is a pragmatic, cluster randomised controlled trial with cost-effectiveness analysis. The study participants are informal caregivers and home-living persons with dementia for whom they care, recruited in various regions in the Netherlands. The trial will compare outcomes in two groups of participants: 85 dyads who receive the intervention, and 85 dyads who receive care as usual. The intervention is a caregiver support training that is manual based and consists of 6 group sessions over 2 months. Training takes place in small groups of caregivers led by a health care professional presented at dementia day care centres. Randomisation occurs at the level of the day care centre. Participants are assessed on the outcome measures at baseline, prior to the intervention, and at 3 and 6 months after baseline.

**Discussion:**

The study will provide insight into effectiveness and cost-effectiveness of an intervention that has not previously been evaluated or implemented in the Netherlands. The intervention potentially adds to the effective support options for informal caregivers of people with dementia without greatly increasing the workload for health- or social care professionals.

**Trial registration:**

The trial is registered at the Dutch Trial Register at NTR6643; August 22^nd^, 2017.

## Background

Currently, it is estimated that there are 50 million people living with dementia worldwide, and this number is expected to increase to approximately 150 million by 2050 (Organization [32]). The majority of people with dementia are cared for by their family members or other informal caregivers at home in the community. As a consequence, they are less likely to be hospitalised or move into residential care and tend to have a better quality of life than those in care homes (Charlesworth, Burnell et al. [5]). However, compared to other caregivers, the informal caregivers of people with dementia experience a greater burden and distress (Ory, Hoffman III et al. [34]). Caring for a person with dementia is described as a chronic stress experience, and caregivers report feeling isolated and overburdened (Szcześniak, Rymaszewska et al. [43]). In the Netherlands, more than half of the caregivers of people with dementia have reported to be quite heavily overburdened, and almost half of the caregivers also reported to be the only one responsible for the care of their loved one or parent (Heide, Veer et al. [19]). The prevalence and incidence of depression and anxiety disorders is high among informal caregivers of older adults, whereas they show less preventive and self-care behaviours, more impairments in physical health, greater acute care utilization, and even increased mortality (Stall, Kim et al. [42]). Van ‘t Leven et al. [50] found that the functioning of the person with dementia was directly related to the functioning of the informal caregiver. As such there is an urgent need to develop interventions for people with dementia and carers that are supportive for both and will improve their quality of life. Multi-component psychosocial interventions combine therapeutic strategies directed at the informal caregiver or the person with dementia or both, and appear particularly effective in improving caregiver well-being, as well as maintaining well-being and daily functioning in the person with dementia (Olazarán, Reisberg et al. [29], Chien, Chu et al. [6], Milders, Bell et al. [25], Van’t Leven, de Lange et al. [50], Sikkes, Tang et al. [39])**.**

Caring for people with dementia living at home is challenging, which is why home-based psychosocial interventions are highly needed to reduce caregiver burden. There is preliminary evidence to support the acceptability of psychosocial interventions for dementia caregivers (Qiu, Hu et al. [35]). For example, it has been found that peer support can significantly improve well-being of caregivers by decreasing feelings of isolation, encouraging better coping strategies, and enabling a change in caregiving behaviour (Brodaty and Donkin [4]), Charlesworth, Burnell et al. [5], (Organization [31]), Sousa, Sequeira et al. [40]). Generally, caregivers often lack social contact and support and experience feelings of social isolation (Brodaty and Donkin [4]), Szcześniak, Rymaszewska et al.[43]), because they lack personal time and opportunities to socialise, and also experience stigma resulting in family and friends distancing themselves (Charlesworth, Burnell et al. [5], Dröes, Meiland et al. [12]). Interventions can offer support to caregivers of people with dementia and can reduce the pressure and distress for the caregiver, which can be of benefit to both the caregiver as well as the person with dementia. Moreover, if nursing home admission of the person with dementia can be postponed (Moon and Adams [27]), the pressure on health and social care services can be reduced (Stall, Kim et al. [42]). Additionally, the costs for long-term residential care of people with dementia could also be reduced, which is important because these are especially high in the Netherlands, and even among the highest in the European Union (Wimo, Jönsson et al. [56]). However, to date there are few effective interventions for caregivers of people with dementia that are widely available. In a review by Sousa et al. (Sousa [41])it was found that the main characteristics of interventions that successfully addressed caregivers’ needs were: (i) six weekly sessions with an average duration of 100 min,(ii) preferred topics ranged from learning and training skills in physical and mental health issues to knowing where to find and how to use available health services; and (iii) greater family and peer support. Based on interviews with caregivers of persons with dementia in different stages of the disease, Boots et al. (Boots [2]) recommended that therapeutic interventions should not be problem-oriented, but instead (i) try to identify the needs of the caregivers’ individual situation, (ii) focus on adaptation rather than on loss, and (iii) increase their knowledge of the disease and future changing roles to reduce the negative consequences of caregiving later on. In turn, caregivers found that the available information on dementia was negative and stigmatizing, and caregivers of persons in more advanced stages of dementia thought that disease-specific knowledge was crucial to help them understand the person with dementia, and improved their ability to empathize with their loved one (Boots, Wolfs et al. [2]).

Although multi-component psychosocial interventions seem to be effective, few attempts have been made to implement these interventions into practice (Gitlin, Marx et al. [14]): translation from randomized trial to implementation into social and support services still seems to be complicated, and large local differences between availability and accessibility of these health care services seem to exist (Birkenhäger-Gillesse, Kollen et al. [1]). A reason for this limited implementation and availability could be the high costs of most current multi-component interventions, and the fact that the interventions rely heavily on already overburdened health care professionals: interventions require time for health care professionals to learn how to present the intervention, but also require time to actually deliver the intervention to caregivers or people with dementia and can in such a way be very labour intensive in practice (Graff, Vernooij-Dassen et al. [16], Milders, Bell et al. [25]). In a recent study by Christie (Christie [7]), it was even found that the implementation of caregiver support programs was often the sole responsibility of a single person within the municipality instead of a team that could tackle implementation issues together. Interventions seemed to have low priority within organisations, even though these were fitting to caregivers’ needs, and incentives or rewards to encourage implementation into clinical practice were often absent (Christie [7]). The authors concluded that implementation needed more engagement of local health care organizations, and that reflecting on and evaluating the implemented intervention should have more priority in the future (Christie [7]).

Therefore, in the current study, a caregiver support program to promote activities at home for people with dementia will be adapted for use and implemented in community based social service settings in the Dutch health care system and evaluated on its effectiveness and cost-effectiveness. To reduce staff costs and demand on health services, this study involved informal caregivers of people with dementia to present part of the intervention and recruited staff from local health care and welfare organizations to train the caregivers. The intervention was manual based to limit the time required for staff to prepare the sessions, and also increase information availability for the caregivers and promote treatment fidelity and compliance with the intervention. The intervention in this study, the so called MOMANT caregiver support program, combines two approaches to caregiver support: first, it is a multi-component intervention aimed at both the person with dementia and the caregiver, using evidence-based components of caregiver support, such as education, peer support, and activity engagement. Previous studies have shown that training family caregivers to present interventions is feasible and acceptable for both people with dementia and caregivers (Teri, Logsdon et al. [46], Quayhagen [36], Gitlin, Winter et al. [15], Milders, Bell et al. [26], Milders, Bell et al. [25]). Trials of combined multicomponent interventions have shown their effectiveness at improving caregiver well-being and postponing institutionalization of the person with dementia with several months to a year (Dröes, Breebaart et al. [11], Olazarán, Reisberg et al. [29], Chien, Chu et al. [6], Van't Leven, Prick et al. [49]). Second, to promote effective implementation of the intervention the informal caregivers are trained to engage the person with dementia in stimulating activities. Previous research showed that this approach can have positive effects on the wellbeing of the caregiver and the person with dementia, as well as on the cognitive functioning of the person with dementia, and it can even improve sense of competence of the caregiver (Teri, Gibbons et al. [44], Onder, Zanetti et al. [30], Graff, Vernooij-Dassen et al. [16], Orgeta, Leung et al. [33]).

### Aim

The main aim of the study is to investigate whether an intervention to educate and train caregivers and to empower caregivers to engage the person with dementia in stimulating activities at home, is effective and cost-effective to improve quality of life in the caregiver and the person with dementia in comparison with usual care; and as such the intervention might be able to contribute to the availability and accessibility of health care services. A further aim will be to investigate whether this intervention can improve caregivers’ feeling of competence, experience of caregiving, and mood.

## Methods

### Design

The study design is a cluster randomized controlled trial. The trial will compare outcomes in two groups of participants: 1) caregivers who receive the intervention and the person with dementia for whom they care; 2) caregivers and the person with dementia for whom they care, who continue to receive usual care. The intervention will be implemented at community day care centres, support centres- and Meeting Centres for people with dementia and carers (hereinafter summarized as day care centres). Randomisation will occur at the level of the centre. Participants recruited at day care centres allocated to the intervention condition will receive the MOMANT caregiver support program, and participants recruited at day care centres allocated to the control condition will continue to receive usual care. Data are collected at baseline, and at 3 and 6 months after baseline.

### Setting

The MOMANT project (registered at the Dutch Trial Register; Trial ID, NTR6643) will be coordinated at the Vrije Universiteit Amsterdam and will involve organisations for care and welfare of the elderly from across the Netherlands. Recruitment of participants, and presentation of the intervention in the intervention condition, will take place at the day care centres by staff of the organisation.

### Participants

The study participants will be dyads consisting of an informal caregiver and the person with dementia for whom they care.

#### Eligibility criteria

Informal caregivers can be spouses, relatives, or friends who care for and support the person with dementia without receiving payment for performing care. If the caregiver does not live with the person with dementia, they have to visit the person with dementia at least 3 times a week to be eligible for the study.

The person with dementia is living at home, cared for by the caregiver, and should have a formal diagnosis of dementia or experience severe cognitive impairments influencing their daily functioning such that dementia is strongly suspected. Type of dementia is not an inclusion criterion. The person with dementia did not start with dementia-specific medication less than 6 months before inclusion.

Exclusion criteria for both the caregiver and the person with dementia will be major mental or physical illness, such as major depression or stroke, that would affect their ability to participate in the training, the intervention or complete the assessments. A second exclusion criteria will be participation in another intervention study.

### Recruitment

Participants will primarily be recruited through health care professionals of day care centres, who are already in contact with the target population. Contact will be made through case managers and day-care coordinators, who will notify potential participants about the study and distribute written information about what participation entails. Contact details of potential participants are only passed to the research team with permission of the potential participants.

### Randomisation

Randomisation occurs at the level of the day care centre. The allocation schedule is produced by a computer-generated random sequence. All dyads recruited at a centre will enrol in the condition to which the centre has been allocated.

### Sample size

The sample size estimation is based on the primary outcome measures of the caregivers and the persons with dementia. At least 64 dyads in each group are required to achieve 80% power to detect significant differences between groups of half a standard deviation on the primary outcome measures using independent sample analyses with an alpha level of 0.05 (Cohen [9]). This estimate assumes a medium effect size (Cohen’s d = 0.5) on the main outcome measures, which is based on effect sizes from comparable interventions in caregivers with an average effect size of d = 0.41 (Olazarán, Reisberg et al. [29]). With an anticipated drop-out rate of 25%, 85 dyads would need to be recruited in each group to end up with 64 dyads completing the study, which is why the aim is to recruit 170 dyads in total.

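### The 80% power claim is not supported as written: the sample size has no design effect although centres are randomised, and d = 0.5 is attributed to an average effect of 0.41

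*Protocol article*

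**What the plan says.** The Sample size section of the protocol article states: "At least 64 dyads in each group are required to achieve 80% power to detect significant differences between groups of half a standard deviation". The test behind this figure is named as an independent-samples one, at alpha 0.05. The section allows for 25% drop-out, which takes 64 completing dyads to 85 recruited per group and 170 in total. No other inflation is applied. On the effect size it says "This estimate assumes a medium effect size" (d = 0.5), described as "based on effect sizes from comparable interventions in caregivers with an average effect size of d = 0.41".

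The Randomisation section says "Randomisation occurs at the level of the day care centre", and that every dyad from a centre joins that centre's condition. The Design section calls the study a cluster randomised trial. The data management and statistical analysis section plans linear mixed models to deal with clustered data, and adjustment for baseline scores. The Intervention section has caregivers trained in groups of 4 to 8. The article gives no ICC, number of centres or number of dyads per centre.

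**The concern.** Two inputs to the only power statement conflict with the rest of the article.

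First, dyads from one centre share a condition and, in the intervention arm, are trained together. Their outcomes may be correlated, and any positive correlation makes 64 dyads worth fewer than 64 independent ones. The calculation treats them as independent.

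Second, the planning effect is 0.5 / 0.41 = 1.22 times the average it is said to come from, and no reason is given for the increase. The cited effects are for caregivers, yet the same d also serves the primary outcome of the person with dementia.

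At stake is how a null result is read. A reader who takes the 80% at face value would treat such a result as stronger evidence against a half-SD effect, or against an effect of the size seen before, than this calculation can support.

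**Working it through.** **Inputs from the article:** 64 completers per arm, d = 0.5, cited average d = 0.41, alpha 0.05, drop-out 25%. Sidedness is not stated; two-sided reproduces the figure, while one-sided would need only about 51 per arm.

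**Assumed inputs (not in the article):** analysed dyads per centre m = 4 to 8, borrowing the training-group size as a proxy; ICC 0.01 to 0.10; baseline to follow-up correlation r = 0.5.

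**Step 1, the plan's own figure.** Two-sample t-test, noncentrality d × √(n/2), df = 2n − 2. With n = 64 and d = 0.5 the noncentrality is 0.5 × √32 = 2.83 and power is 80.1%. The n for exactly 80% is 63.8, rounded up to 64. So 64 is the individually randomised size with a design effect of 1. Drop-out: 64 / 0.75 = 85.3, strictly 86 against the stated 85; 85 × 0.75 = 63.75. That difference is trivial.

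**Step 2, the cited effect with independent dyads.** n = 64 and d = 0.41: noncentrality 0.41 × √32 = 2.32, power 63.4%. Reaching 80% takes 95 completers per arm, or 95 / 0.75 = 126.7, so 127 recruited per arm. Even if all 85 recruited dyads per arm were analysed, power would be 76%. This step needs no outside assumption.

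**Step 3, clustering.** Design effect DE = 1 + (m − 1) × ICC and effective n = 64 / DE. The difference detectable with 80% power is about 0.5 × √DE.

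**Step 4, baseline adjustment.** The outcome variance is multiplied by 1 − r² = 0.75, so effective n = 64 / (DE × 0.75) and the detectable difference is about 0.5 × √(DE × 0.75). This takes the ICC as unchanged by the adjustment.

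| m, ICC | DE | Effective n, unadjusted / r = 0.5 | Power at d = 0.5, unadjusted / r = 0.5 | Power at d = 0.41, unadjusted / r = 0.5 | Detectable d, unadjusted / r = 0.5 |
|---|---|---|---|---|---|
| 4, 0.01 | 1.03 | 62.1 / 82.8 | 79% / 89% | 62% / 75% | 0.51 / 0.44 |
| 6, 0.05 | 1.25 | 51.2 / 68.3 | 71% / 83% | 54% / 66% | 0.56 / 0.48 |
| 8, 0.10 | 1.70 | 37.6 / 50.2 | 57% / 70% | 42% / 53% | 0.65 / 0.56 |

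**Step 5, sensitivity.** If degrees of freedom are counted at centre level (m = 6 gives 64 / 6, about 11 centres per arm and about 20 df), the middle row falls to about 67% and 50% unadjusted, and to about 79% at d = 0.5 with r = 0.5. In the same row with dyad-level df, 80% power at d = 0.41 needs an effective n of 94.4. That means 1 − r² = 51.2 / 94.4 = 0.54, so r is about 0.68.

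**The case against.** The case on the other side has real weight. The arithmetic is right for the inputs used. The 80% is conditional on d = 0.5, and 0.41 is openly printed beside it. The mixed model deals with clustering in the analysis, so tests and intervals need not inherit the omission. Baseline adjustment is planned, and with r = 0.5 it can carry power at d = 0.5 back above 80%. The clustering loss depends on an ICC and cluster size that the article does not report, and training-group size is not cluster size. At ICC 0.01 the loss at d = 0.5 is only 1 to 3 points. Data collection was expected to be complete by December 2021, before publication, so enrolment cannot sensibly be reopened.

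Most of this limits the claim without removing it. A mixed model gives valid standard errors but does not restore the information lost to clustering. The sample size neither states nor uses a baseline correlation, so the gain from adjustment cannot be credited to its 80%. A condensed article may leave out an ICC, but this one says which method was used, and that method does not match the design. Printing 0.41 does not explain why 0.5 is based on it.

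A reader might infer something stronger: that the trial fails to reach 80% power, or that its power is really about 50 to 60%. The article supports neither. At d = 0.5, power falls on either side of 80% depending on unreported values. The 50 to 60% figure belongs to unadjusted cases at d = 0.41 and ignores the planned baseline adjustment.

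**Conclusion.** The 80% power is not supported as written. It is the power of an individually randomised t-test at d = 0.5, applied to a cluster trial, with an effect size larger than its stated and caregiver-only basis. The one shortfall that follows from the article's own figures is 63% in place of 80% at d = 0.41, before clustering or baseline adjustment. Everything beyond that is a sensitivity range. For m = 4 to 8 and ICC 0.01 to 0.10, unadjusted power is about 79% to 57% at d = 0.5 and 62% to 42% at d = 0.41. With an assumed baseline correlation of 0.5 it is about 89% to 70% and 75% to 53%. At the cited effect, 80% is out of reach throughout these ranges; a higher correlation (about 0.68 at m = 6 and ICC 0.05) would be needed. At d = 0.5 the question stays open. The fault lies in the inputs and their justification, not in the arithmetic, and the planned estimates and tests are unaffected.

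**What to change.** Keep 170 dyads and restate the Sample size section, or correct it in the results report, as follows:

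- Give the design effect 1 + (m − 1) × ICC with the actual mean number of analysed dyads per centre, the number of centres, and an ICC range such as 0.01 to 0.10.
- If the gain from baseline adjustment is to be claimed, show the factor 1 − r² under a stated correlation.
- Report the resulting power at both d = 0.41 and d = 0.5, and the difference detectable with 80% power.
- Either give a reason for planning on 0.5 or drop the statement that it is based on 0.41.
- Note that the cited effect comes from caregivers only, so it gives no direct support for the outcome of the person with dementia.

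The cost is rewording and a less favourable stated power. No extra enrolment and no change to the analysis is needed.
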